## Abstract

**Trial registration:**

German Clinical Trials Register (DRKS) DRKS00031355. Registered on April 5^th^ 2023.

**Patient or Public Contribution:**

Patient representatives contributed to the development of the AI‐based application through the use of Delphi methodology, as part of the KIADEKU qualitative sub‐study.

AbbreviationsAEAdverse EventAIArtificial IntelligenceBMBFGerman Federal Ministry of Education and ResearchDRKSGerman Clinical Trials RegisterEPUAPEuropean Pressure Ulcer Advisory PanelGLOBIADGhent Global IAD Categorization ToolIADIncontinence‐associated dermatitisIKIMInstitute for Artificial Intelligence in MedicineKIArtificial Intelligence (German abbreviation)KSHKatholische Stiftungshochschule Munich University of Applied SciencesLMULudwig‐Maximilians‐University MunichMITDepartment of Medical Technology and IT at LMU University HospitalPIPressure InjurySAESerious Adverse Event

## Background

1

Artificial Intelligence (AI)‐based applications are increasingly used in clinical wound management, and show substantial potential for enhancing wound assessment, care, and treatment. They offer benefits such as standardized wound images, accurate wound measurements, identification of wound complications, support for classification and treatment decisions, and efficiencies in documentation (Dabas et al. 2023; Lau et al. 2022; Mohammed et al. 2022). However, most research primarily focuses on physicians as the end‐users of these applications, often overlooking the nursing perspective. These AI‐based applications are powered by AI models trained on large datasets to autonomously identify patterns and make predictions or decisions. The models use various algorithms and network architectures, frequently combining multiple models to improve performance.

Pressure injuries (PI) are a globally recognized clinical issue and a key indicator of quality in nursing care (European Pressure Ulcer Advisory Panel, National Pressure Injury Advisory Panel, & Pan Pacific Pressure Injury Alliance 2019; Gemeinsamer Bundesausschuss 2023). Without timely and effective treatment, PIs can lead to severe patient and economic burdens, including extended hospital stays and increased healthcare costs (Labeau et al. 2021).

Incontinence‐associated dermatitis (IAD) results from prolonged exposure to urine or feces, leading to skin inflammation (Gray et al. 2007). It is a prevalent condition among patients with incontinence in acute care, with studies reporting a prevalence of 42% to 45.7% (Campbell et al. 2016; Gray and Giuliano 2018). Clinically, IAD manifests as erythema, potentially accompanied by skin loss, and can include skin infections such as candidiasis (Gray et al. 2007). Pressure injuries, on the other hand, can range from non‐blanchable erythema with intact skin to complete skin destruction, extending through subcutaneous fat, muscle, and even bone (European Pressure Ulcer Advisory Panel, National Pressure Injury Advisory Panel, & Pan Pacific Pressure Injury Alliance 2019).

The visual similarities between IAD and PI, particularly in their early stages and common gluteal location, frequently lead to uncertainty and misclassification in nursing practice (Beeckman et al. 2008; LeBlanc et al. 2016). Despite the availability of validated assessment tools like the European Pressure Ulcer Advisory Panel (EPUAP) guidelines (European Pressure Ulcer Advisory Panel, National Pressure Injury Advisory Panel, & Pan Pacific Pressure Injury Alliance (2019)) and the Ghent Global IAD Categorization Tool (GLOBIAD), differentiating between these wound types remains a challenge for nurses (Beeckman et al. 2017, 2018; Francis 2019). Furthermore, studies suggest that nurses often possess limited knowledge about IAD (Barakat‐Johnson et al. 2022; Zhang et al. 2021), and misconceptions in assessing these wounds can lead to inappropriate intervention choices and delays (Beeckman et al. 2010). Beyond these assessment difficulties, challenges in wound documentation also persist. Research indicates that wound documentation frequently fails to capture all details of the assessment and care (Do et al. 2021; Gillespie et al. 2014; Li and Korniewicz 2013; Topaz et al. 2016). Issues such as irregular wound shapes, localization, and identifying exact wound margins can complicate measurement accuracy (Haghpanah et al. 2006; Keast et al. 2004). The use of low‐tech tools like paper rulers and depth probes often results in poor interobserver reliability and measurement inaccuracies (Haghpanah et al. 2006; Keast et al. 2004; Wang et al. 2017). Additionally, wound documentation is time‐consuming, particularly when photographing wounds. Digital cameras are employed for this purpose in clinical nursing practice at LMU University Hospital, and uploading these images to electronic patient records is often tedious and can be delayed by up to 2 days or more.

In other nursing areas, AI‐based technologies are already being used to support evidence‐based nursing practices (Ronquillo et al. 2021). Common challenges include a lack of technical and informatics skills (Abuzaid et al. 2022; Gerich et al. 2022) as well as ethical concerns (Robert 2019). To overcome these challenges and ensure AI applications are optimally adapted to the needs of professional nurses, it is crucial to involve nurses in the research and development processes (Gerich et al. 2022; Zhou et al. 2021). This involvement can greatly enhance the utility of AI for nurses and lead to improved patient care outcomes.

In the KIADEKU (KI^1^‐IAD‐DEKUbitus^2^) research and development overall project (German Clinical Trials Register number (DRKS00029961)), we are developing an AI‐based application for digital image analysis of PI and IAD. This development is based on nursing‐relevant questions and is being conducted in cooperation with the Institute for Artificial Intelligence in Medicine (IKIM). As illustrated in Figure 1, the overall project encompasses a technical sub‐study, a qualitative sub‐study, and the controlled clinical intervention sub‐study described in this study protocol.

**Figure 1 nur22469-fig-0001:**
[figure not shown]
KIADEKU Overall project and sub‐studies.

To develop the AI model in the technical sub‐study, a literature‐based minimal data set for wound documentation of PI and IAD was defined. Based on this, 1,555 existing wound images and associated characteristics were extracted from the hospital information systems of two German university hospitals. The study team validated, segmented, and annotated these images and characteristics, achieving consensus on wound type and classification. Subsequently, four AI network architectures were evaluated, and the model with the best performance for differentiating between PI and IAD was selected. This transformer‐based model's performance was systematically enhanced through additional methods of data pre‐ and post‐processing, augmentation techniques, and training methods. The performance of the developed AI model for binary differentiation of PI and IAD and wound classification was evaluated using accuracy and F1 score (Harmonic Mean of Precision and Recall) on a test data set. These processes are described in more detail in the technical sub‐study conducted by the Institute for Artificial Intelligence in Medicine (IKIM).

After the AI model training was completed, we integrated it into the WUNDERA® wound documentation application of the project partner sciendis GmbH and it is now being used in the clinical intervention sub‐study to assist nurses in differentiating, assessing, and documenting PI and IAD wounds, and to facilitate personalized, evidence‐based nursing interventions. In a further qualitative sub‐study, the project partners at University Hospital Essen involve patients, wound experts, and nurses from both hospitals in the development of the AI, exploring their experiences and perspectives on the AI‐based application using group Delphi methodology and case vignettes.

The objective of this controlled clinical intervention sub‐study is to assess the quantitative effects of the AI‐based digital wound management application, which was fully developed in the technical sub‐study, on nurses’ wound assessment, care, and documentation. This evaluation focuses on the duration of wound assessment, dressing changes and documentation, the task load of nurses, and guideline adherence compared to conventional care in a non‐randomized pre‐post intervention study. Additionally, we will determine the accuracy of the AI‐generated predictions of wound type and wound classification in the clinical setting, as well as the usability of the AI‐based application.

## Method and Design

2

### Objectives

2.1

The primary objective of this sub‐study is to explore the relationship between the use of the AI‐based application and several factors: the duration of wound assessment, dressing changes, and documentation; the nurse's task load; and adherence to guidelines. We will adjust for potential covariates such as wound severity, the nurse's professional experience, and the general workload of the shift. A secondary objective is to evaluate the accuracy of the AI predictions regarding wound type and classification in a clinical setting, as well as the usability of the AI‐based application and standard clinical documentation systems.

Our hypothesis, which we intend to test, is that the use of the AI‐based application will enhance the differentiation, assessment, and documentation of PI and IAD by reducing the time required for wound assessment, dressing changes, and documentation; lowering nurses’ task load; and improving guideline adherence.

### Ethics Approval and Consent to Participate

2.2

The study has received approval from the Ethics Committee of the LMU Medical Faculty (process number 22‐0970), the Data Protection Officer of LMU Hospital (process number 1952) and the Staff Council of LMU Hospital. All procedures will be conducted in accordance with the Declaration of Helsinki, and any significant changes to the study protocol will require re‐approval from both the Ethics Committee and the Data Protection Officer. We will ensure compliance with all Ethics Committee requirements and obtain informed consent from all participants before enrollment. Should adjustments to the study protocol become necessary during the study, the study registration will be updated accordingly.

### Design

2.3

The study is designed as a monocentric, non‐randomized, controlled pilot intervention study with a pre‐intervention data collection period followed by a data collection period during the deployment of the AI‐based application (intervention) on the wards. Due to the nature of the intervention, it is not possible to blind either participants or observers.

In the pre‐intervention phase, we observe the wound care and documentation for PI and IAD according to hospital standards in the control group, using a standardized observation form, and survey the nurse using a standardized questionnaire (Figure 2). In the subsequent intervention phase, we train the nurses in the intervention group to use the AI‐based application, then observe and survey the wound care and documentation supported by the AI‐based application, consistent with the procedures used in the pre‐intervention phase (Figure 2). The reporting of the study protocol is based on the SPIRIT AI extension (Cruz Rivera et al. 2020).

**Figure 2 nur22469-fig-0002:**
[figure not shown]
KIADEKU controlled clinical intervention sub‐study flow diagram.

### Setting

2.4

We are conducting the study at LMU University Hospital, a center renowned for its high‐end medicine, nursing, medical innovation, and research. With over 2,000 beds, LMU Hospital is a highly advanced hospital that encompasses all fields of medicine.

For this study, we selected four intensive care units, one intermediate care unit, and three general wards. These wards were chosen due to their notably high incidence of patients with pressure injuries (PI) or incontinence‐associated dermatitis (IAD), reflecting the specific diseases treated and the demographics of their patient populations. These wards differ in terms of medical specialty and the number of staff, ranging from 33 to 54 employees (average 45.8) in the intensive care and intermediate care units, and from 15 to 28 employees (average 23) in the general wards. The nursing and ward managers agreed to participate in this study. In addition, consent was obtained from the Staff Council, the Data Protection Officer, and the Ethics Committee of the LMU Medical Faculty. Additionally, before the commencement of the study, we confirmed that the selected wards had adequate Wi‐Fi coverage to support the use of the AI‐based application on tablets and smartphones.

### Participants and Eligibility Criteria

2.5

The study sample comprises adult volunteer nurses providing PI and IAD care for newly occurring wounds or pre‐existing wounds from newly admitted patients on the participating wards. Since IAD occurs solely in the pelvic area and the AI specifically aids in differentiating between the two wound types, only wounds located in the pelvic area are considered. All participating nurses must be fluent in German and are required to sign informed consent documents as part of the ethical clearance process. Exclusions apply to wound care for other types of wounds, patients under the age of eighteen, wounds outside the pelvic area, and patients who, according to the nurse's assessment, are in the preterminal or terminal phase. We also exclude intensive care patients who are too unstable for positioning for wound care or for whom life‐sustaining measures are being terminated. Additionally, nurses who do not give informed consent, do not speak fluent German, or are non‐registered nurses, trainees, and interns are excluded.

The inclusion and exclusion criteria for data used in AI training are detailed in the technical sub‐study conducted by the Institute for Artificial Intelligence in Medicine (IKIM). The input data for AI prediction includes the wound image captured in the application and additional patient data (such as immobility, incontinence, and sensibility assessments) entered by the nurse. Images are reviewed for suitability for prediction (e.g., exposure, image clarity), and, if necessary, users are requested to capture a new wound image.

### Sample Size

2.6

Based on current methodologies, we performed an a priori sample size calculation using power analysis (Döring and Bortz 2016) with the G*Power 3 software (Faul et al. 2007). For this calculation, we assumed moderate effect sizes between dependent and independent variables (Cohen 1988), an alpha level of 0.05, and a power of 0.80. To test correlations between dependent variables (task load, time, guideline adherence) and four independent variables (use of the demonstrator, general load of the shift, professional experience, severity of wound) using multivariate models (multiple linear regression) under these assumptions, we will require a total of 85 nurses.

With a calculated sample size of 85 nurses and considering up to four independent variables, we anticipate obtaining meaningful results within a manageable timeframe and with the available resources. Accounting for a projected 10% dropout and missing rate, based on experiences from previous studies, we plan to recruit 95 nurses to ensure a sufficiently large sample for subsequent evaluation.

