### Recruitment

2.7

A dedicated electronic wound reporting system will be utilized to identify wounds that meet the inclusion and exclusion criteria. Due to the absence of an electronic reporting system for IAD and the likelihood that many wounds are not electronically documented, the research team will contact the included wards daily by telephone. They will inquire about new cases of PI or IAD or the admission of patients with existing PI or IAD wounds. Each patient is only included once in the study.

If wounds that meet the inclusion and exclusion criteria are identified, the study team will arrange for the next scheduled wound care appointment. At this appointment, the study team will inform the patient's nurse about the study. If the nurse in charge declines participation, no observation or survey will be conducted at that time. Still, the patient may be re‐enrolled at the next wound care appointment if the subsequent nurse agrees to participate. If the nurse consents in writing to participate, the study team will proceed with the observation of wound care and documentation. After completing the wound documentation, the nurse will complete an online questionnaire on a tablet, which includes questions about demographic data, general workload of the shift, task load, and the usability of the documentation system used. The study primarily targets new wounds and newly admitted patients with wounds. Due to organizational factors, there may be delays in some cases, including weekend admissions, nurses refusing to participate, and delayed documentation of new wounds.

To encourage participation, we engaged local wound experts and ward managers in the development of the digital system in the KIADEKU qualitative sub‐study and as key users during its implementation on the wards to enhance user acceptance. Additionally, nurses who agree to participate will receive vouchers as compensation for the extra effort involved in the study. These measures are anticipated to help achieve the sample size determined by the a priori sample calculation.

After careful consideration, obtaining patient consent was deemed unnecessary. This decision was based on the fact that wound management in the study aligns with standard practice, with the only variation being the documentation tool used. Furthermore, the study does not collect data that could identify patients. Nonetheless, the study team informs patients about the study before administering wound care.

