During wound care, the nurse will use a tablet or smartphone to take a picture of the wound and enter additional patient information, such as incontinence status, sensibility, and mobility. The AI checks the image's suitability for prediction based on exposure and definition. If the image quality is deemed inadequate, the system prompts the user to retake the image. The application does not request any personal patient information that would allow identification, such as name, date of birth, or case number. The AI‐based application automatically measures the wound using a patch as a reference point, and predicts the wound type, classification, and documentation characteristics based on the wound image and additional patient data. Additionally, the system displays the AI‐calculated probability for each characteristic. The nurse reviews and, if necessary, revises the AI's predictions to ensure accurate wound documentation and appropriate subsequent interventions. Optionally, the application suggests nursing interventions from the hospital's existing wound care standard operating procedures relevant to the documented wound type and characteristics. In additional information fields, the AI‐based application provides detailed descriptions and definitions of wound types (e.g., EPUAP and GLOBIAD classifications) and further information on in‐house wound management standards (e.g., contraindications or user instructions for specific wound dressings).

The primary difference between the standard documentation system and the AI‐based application is that photography and documentation are conducted on‐site using tablets and smartphones, unlike in standard care where documentation occurs post‐care using fixed PCs and digital cameras. Additionally, in the AI‐based application, the wound is automatically measured, and the wound type and characteristics are pre‐populated by the AI model based on the wound image, which then must be validated and revised by the nurse if necessary. In contrast, the standard systems only offer the option of using the last known values. Furthermore, the AI‐based application provides additional information such as wound severity categories and appropriate nursing interventions for the documented wound, features that are absent in the standard system.

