Potential challenges in implementing the AI‐based application in a clinical setting include technical issues, such as ensuring full Wi‐Fi coverage, and meeting hygiene requirements, such as disinfecting tablets. Another common hurdle in technology intervention studies is user acceptance. However, in the realm of technologies that support nursing tasks, studies have shown high technology acceptance (Zöllick et al. 2020). We therefore anticipate high acceptance due to the simplification of wound care and documentation processes. To further enhance user acceptance, local wound experts and ward managers have been involved in the development of the application and will be key users during its implementation on the wards. Additionally, the implementation will be supported by comprehensive training measures to ensure safe use and handling of the application and AI predictions. This is crucial, especially when addressing incorrect or inaccurate predictions made by AI and the ethical challenges that arise in biomedical AI (Mittelstadt et al. 2016).

As this study is monocentric, focusing only on nurses at one university hospital, the external validity is limited. Another limitation is the constrained resources of the project, which preclude the use of a randomized study design and may introduce slight biases due to the consecutive and non‐randomized observation of control and intervention groups, as well as the absence of blinding. Moreover, the organization of information events and recruitment of nursing staff may heighten awareness of pressure injury and IAD care, potentially influencing care and documentation and thus the results of the study. Organizational delays, which are inevitable due to clinical processes, may also introduce bias. We also acknowledge that factors such as ward affiliation might influence outcomes, but were not included in this exploratory pilot study due to the complexity of the models required and the limited sample sizes. For this reason, only the most crucial factors, from an expert perspective, were included in the analysis.

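### The duration and task-load models name no wound-type term, so a difference in PI/IAD mix between the two phases may be read as an effect of the AI application

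*Protocol article*

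**What the plan says.** **Model terms.** The Sample Size section lists "four independent variables (use of the demonstrator, general load of the shift, professional experience, severity of wound" and speaks of at most four such variables. The Analysis Plan fits a separate linear regression for each outcome, naming the same three covariates beside demonstrator use. It presents them as examples, and it dummy codes severity. Neither section names wound type. The article does not say on what scale severity is graded across PI and IAD.

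**Design.** The study is single-centre, non-randomised and pre-post. Control data were collected from May 2023 to January 2024, and intervention data from July 2024 (Data Collection and Management).

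**Case finding.** Eligible wounds are sought through an electronic reporting system. The Recruitment section says that this system does not cover IAD and probably misses many other wounds, so "the research team will contact the included wards daily by telephone. They will inquire about new cases of PI or IAD".

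**What differs by phase.** In the intervention phase nurses are trained on the application, which also "provides detailed descriptions and definitions of wound types" (Intervention). The Discussion accepts that information events and recruitment "may heighten awareness of pressure injury and IAD care, potentially influencing care and documentation and thus the results of the study". It does not mention the PI/IAD mix.

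**Reference assessment.** A study-team member assesses wound type and classification on site, independently of the nurse and the AI (Measures).

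**The concern.** Every control observation comes from the first period and every intervention observation from the second. The demonstrator coefficient is therefore also the phase coefficient. Any difference between phases in the kind of wound observed goes into it unless a covariate takes it out.

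Wound type is an obvious candidate. The study is about telling PI from IAD, and it restricts eligibility to pelvic wounds for that reason. IAD cases depend mainly on what wards report by telephone. The mix could change with awareness, or simply because the two periods differ in season and patients.

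Severity as one covariate need not close the gap. The article cites two classification systems, EPUAP for PI and GLOBIAD for IAD. If severity is coded by the categories of both systems, its dummies also identify wound type. If it is coded on a common grade, they do not. At stake is whether an apparent change in time or task load reflects the application or a different mix of wounds.

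**Working it through.** **1. The plan's own sample size.** The inputs are "an alpha level of 0.05, and a power of 0.80" and, for the effect, "we assumed moderate effect sizes between dependent and independent variables". The value is not printed, so I take Cohen's f² = 0.15. For the omnibus F-test with p = 4 predictors:

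- noncentrality λ = f² × N = 0.15 × 85 = 12.75
- degrees of freedom 4 and 85 − 4 − 1 = 80
- power = 0.803, and 85 is the smallest N that reaches 0.80

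This agrees with "we will require a total of 85 nurses". "Accounting for a projected 10% dropout and missing rate", 85 / 0.9 = 94.4, rounded up to 95, the stated recruitment target. The sample size is not in error.

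**2. Possible bias from an omitted wound type.** If severity absorbs none of the shift:

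bias (in SD) = (change in IAD share between phases) × (IAD-PI difference in outcome, in SD)

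The documents give neither factor, so both are assumed. I also assume an equal split of the 85 nurses (43/42), which the article does not state. The standard error of the coefficient is then √(1/43 + 1/42) = 0.217 SD, with 80 degrees of freedom. The last column uses the noncentral t distribution with noncentrality bias / 0.217.

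| Share shift | IAD-PI difference (SD) | Bias (SD) | Chance of p < 0.05 with no true effect |
|---|---|---|---|
| none | any | 0 | 5.0% |
| 10 points | 0.5 | 0.05 | 5.6% |
| 20 points | 0.5 | 0.10 | 7.4% |
| 20 points | 0.8 | 0.16 | 11.3% |
| 30 points | 0.8 | 0.24 | 19.4% |
| 30 points | 1.0 | 0.30 | 27.7% |

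The sign of the bias depends on the signs of both factors. It could create an apparent benefit or hide one.

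**3. Cost of adding terms** (same f², total N = 85)

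| Model terms | Omnibus power at 85 | Omnibus N for 0.80 (recruited at 10% loss) | Power, demonstrator coefficient |
|---|---|---|---|
| 4 (as planned) | 0.803 | 85 (95) | 0.94 |
| 5 (one type term) | 0.764 | 92 (103) | 0.94 |
| 7 (three extra terms) | 0.695 | 103 (115) | 0.94 |

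The last column takes f² = 0.15 as the partial effect of the demonstrator. It treats that effect as unchanged by the added terms.

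**The case against.** A reader might infer that training and the application change case finding by construction, so that a false AI effect is built in. The documents do not support that reading:

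- The training described covers how AI works, use of the application and handling of wrong predictions. No teaching on recognising PI or IAD is described.
- The application is used at the wound care appointment, after the case has been found.
- Confusing PI with IAD does not decide entry, because either label qualifies. Selection needs wounds that go unreported under both labels.
- One case-finding procedure is described for the whole study. The Discussion ties awareness to information events and recruitment, and recruitment and daily calls also ran in the control phase.
- Pressure relief and the separate clock-start rule when no dressing is present do not show that duration differs by wound type. Patient positioning is excluded from the timed interval, and no passage links the presence of a dressing to wound type.

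The authors also disclose possible bias from consecutive, non-randomised observation. They call the study an exploratory pilot and defend a short covariate list on grounds of complexity and sample size. Severity may already be coded so that it carries type, and a full protocol or analysis plan may say so.

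All of this limits what can be claimed about mechanism and size. It does not remove the gap: phase and demonstrator use cannot be separated, the mix can differ for any reason, and no named term is certain to account for it. The complexity argument is weak for one binary covariate that leaves power for the coefficient of interest almost unchanged.

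**Conclusion.** The point holds in a limited form. The models for duration and task load name no wound-type term, and the article does not establish that severity carries wound type. A difference in PI/IAD mix between phases **may** therefore be read as an effect of the application. The documents do not show that such a difference exists, which way it runs, or that the application causes it.

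The illustrative bias of 0.05 to 0.30 SD, with a false-positive rate of 5.6% to 27.7% against a nominal 5%, rests entirely on assumptions: the share shift, the outcome difference, an equal split, and no absorption by severity. The lower end is close to nominal, and the upper end needs both extremes together. If severity is coded by EPUAP and GLOBIAD category, this bias largely disappears. The change is worth making because it is cheap and guards against a mix difference from any cause.

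**What to change.** 1. In the duration and NASA TLX models, add wound type (PI or IAD) as a covariate, taken from the on-site study-team assessment. Alternatively, state that severity is coded as categories within wound type, so that type is carried.
2. Define the severity scale for PI and for IAD.
3. Tabulate wound type and severity by phase. Add notification route only where it was recorded, since the article does not say that it was and control collection has ended.

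**Cost.** This is a change of analysis wording, with one degree of freedom for a type term or a few if severity is coded within type. With one added term, omnibus power at N = 85 falls from 0.80 to about 0.76, and restoring 0.80 would need 92 analysed (103 recruited). Power for the demonstrator coefficient stays at about 0.94. New data should not be needed. Data Collection and Management describes on-site wound assessments without limiting them to one phase, and the adherence criterion on correct wound type needs such a reference in both. The sponsor should confirm that the control-phase assessments are on file.

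**Limit.** Adjustment removes only differences in type and recorded severity. Other differences between the periods remain, and the assessors are not blinded to phase.
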